#### 2.5.1. Case Group (Group A)

This group performs meditation with a virtual reality (VR)/3D (three-dimensional) video: patients watch a 10 min immersive virtual reality video of mindfulness meditation with images and sound in a comfortable chair at the FCECON office, using Samsung^®^ Gear VR virtual reality glasses and a Samsung^®^ smartwatch.

The meditation for Group A consists of watching an immersive 3D virtual reality (VR) video in 360°, entitled “Secret Garden,” where participants can immerse themselves in a beautiful and relaxing Japanese garden, with all the natural elements, such as the flow and sound of running water. This experience was made available by the Italian company BECOME SRL, also known as BECOME. Augmented Life, available at “www.discoverbecome.com”. BECOME SRL is a startup specializing in creating customized virtual reality content and environments for researchers and neuroscientists. The video used in our study was developed especially for this research, with audio in Brazilian Portuguese.

#### 2.5.2. Active Control Group (Group B)

This group performs meditation with 2D video (two-dimensional video): patients watch a simple 10 min video presented via cell phone with image and sound, featuring mindfulness meditation in a comfortable chair in the FCECON office, using a Samsung^®^ smartwatch.

The meditation in Group B consists of watching a 2D video in non-immersive mode on an Android cell phone. Participants in this group then have the opportunity to observe a beautiful and relaxing lake surrounded by a forest to the sound of meditation guided by the psychiatrist, psychotherapist, and mindfulness teacher [name]. This video is part of the video collection used in [name] research and was made available for use in our study.

#### 2.5.3. Passive Control Group (Group C)

This group performs meditation with an audio-guided meditation: Audio for breathing exercises Time 1. Patients perform breathing exercises based on instructions from the healthcare professional for 4 min in a comfortable chair at the FCECON office, using a Samsung^®^ smartwatch.

The meditation in Group C consists of listening to an audio recording in non-immersive mode on an Android cell phone, where participants have the opportunity to perform breathing exercises to the sound of meditation also guided by the psychiatrist, psychotherapist, and mindfulness teacher [name]. This audio recording is part of [name] research audio collection, which was made available for use in our study.

#### 2.5.4. Randomization and Blinding

The randomization is performed by the principal investigator using a specific commercial mobile application called Randomizer^®^ for Clinical Trial Lite, which is a secure, validated application that works with encrypted network traffic using TLS (Transport Layer Security), a strong encryption for random distribution among the research groups.

The study is a comparative study; the participants in the case group, active control group, and passive control group are recruited in the same way, receive the same information about meditation, and answer the same questionnaires before and after meditation. However, given the nature of behavioral interventions (virtual reality and 2D video or audio), both participants and research assistants conducting the interventions cannot be blinded to group allocation. The questionnaires used in the study are administered and collected by researchers who are aware of the intervention modality and are responsible for setting up the equipment, training participants, and providing technical support.

To minimize bias, the statistician responsible for the analyses will remain blinded to group allocation, and group labels will be coded during data analysis. We recognize the lack of blinding of the evaluator as a limitation, which will be considered in the interpretation of the results.

### 2.6. Outcome Measures

The primary outcome of the protocol is the change in pain intensity, measured by the Brief Pain Inventory—Short Form (BPI), from the beginning of the study (T1) to the eight-week follow-up (T3). The item “worst pain in the last 24 h” (numerical scale from 0 to 10) will be used as the indicator of pain intensity, as it has been validated and demonstrated to be clinically important in oncology and palliative care populations.

Secondary outcomes will encompass metrics designed to assess the psychological, functional, and symptomatic domains. Psychological morbidity will be assessed using the Hospital Anxiety and Depression Scale (HADS), including total and subscale scores. Quality of life will be evaluated using the McGill Quality of Life Questionnaire.

In addition to longitudinal assessments at T1 (baseline), T2 (four weeks), and T3 (eight weeks), the immediate pre- and post-intervention effects will be explored using the Edmonton Symptom Assessment Scale (ESAS). The ESAS will be administered prior to and following each in-person guided meditation session to assess acute changes in symptoms. Pain intensity, severity, and interference will be measured using the respective subscales of the BPI. The extent to which participants adhere to the intervention will be determined by calculating the percentage of prescribed meditation sessions completed during the follow-up period.

The subsequent Table 3 offers a synopsis of all outcome measures, variables, analysis metrics, aggregation methods, and assessment time points.

## 3. Statistical Analysis

### 3.1. The Sample Size

The sample size was determined based on the estimated number of approximately 140 patients monitored monthly at the FCECON Pain Therapy and Palliative Care Service. In the absence of prior evidence to facilitate reliable estimates of effect size, variance, or intra-participant correlation for comparisons between immersive virtual reality, 2D video, and guided meditation in adults with cancer-related pain receiving palliative care, a formal power-based calculation could not be conducted. Consequently, the sample size was determined using a feasibility-based approach. In the context of palliative oncology, where recruitment is inherently limited and attrition rates are high, using the average monthly number of eligible patients to determine sample size is an appropriate strategy.

The sample calculation was performed using G*Power 3.1 software. For the calculation, an effect size of 71% was considered for three groups. For the remaining parameters, a significance level of 5% and a sample power of 96% were adopted. These parameters were also defined for the three groups, under the assumption that there would be three measurement moments and that the analyses would be performed in SPSS (version 29.0).

The sample size was determined to be 39 participants per group. Consequently, the total number of participants would be 117, categorized into three groups of 39 participants each. Furthermore, considering the possibility of loss to follow-up, 12% was added to the final value of 39 participants, resulting in a final sample of 129 participants.

The final sample size was divided into three groups: an experimental group (Group A), a passive control group (Group B), and an active control group (Group C). The total number of participants in each group was 43.

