### 3.2. Analysis

Descriptive statistics are applied to characterize patients at baseline. Continuous variables are reported as the mean and standard deviation, while categorical variables are expressed as frequency and percentage. To analyze the longitudinal data of the three groups, repeated-measures ANOVA is used to define the impact of each intervention on the three paired groups of participants. The response variable, which is mindfulness meditation through virtual reality, is analyzed over time, comparing the three groups. If we do not have a normal sample, we will perform the analysis of Generalized Estimating Equations (GEEs), a semi-parametric method to test the differences between groups and the interaction of variables and groups over time.

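### Section 3.1 says no formal power calculation was possible, then reports one, and its 39 per group at 96% power cannot be reproduced from the stated inputs

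*Protocol article*

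**What the plan says.** Section 3.1 of the protocol article gives two accounts of how the sample size was set.

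- **Feasibility.** The size rests on patient flow: "The sample size was determined based on the estimated number of approximately 140 patients monitored monthly". The reason is given as "In the absence of prior evidence to facilitate reliable estimates of effect size, variance, or intra-participant correlation", and the conclusion is that "a formal power-based calculation could not be conducted".
- **Power.** The following paragraph states "The sample calculation was performed using G*Power 3.1 software". Its inputs are "For the calculation, an effect size of 71% was considered for three groups", then "a significance level of 5% and a sample power of 96% were adopted", for three groups and "under the assumption that there would be three measurement moments". The result is 39 per group (117 in total), raised for losses of 12% to 129, or 43 per group.

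The article does not give the effect-size metric, the G*Power test, the correlation or the source of the 71%. Section 3.2 names the analysis: "repeated-measures ANOVA is used to define the impact of each intervention". Section 2.6 defines the primary outcome as the change in BPI worst pain from T1 to T3.

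**The concern.** If effect size and correlation could not be estimated, a repeated-measures power calculation had no inputs. If they could, the feasibility paragraph is wrong. Both accounts stand in the current text of one section.

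ANOVA and t-test power calculations do not express effect size as a percentage, so the reader must guess what 71% means. The two obvious guesses, f = 0.71 and d = 0.71, miss 39 per group in opposite directions, so rounding does not explain the gap.

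The 96% is the article's only statement of what the trial can detect. The Discussion (section 4) reports that earlier VR interventions were not superior to 2D-screen equivalents, so a result showing no difference between Groups A and B is plausible. That result might then be judged against a power figure that cannot be traced.

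**Working it through.** **Inputs from sections 3.1 and 3.2.** k = 3 groups, m = 3 visits, alpha 0.05, power 0.96, 71% read as 0.71, stated result 39 per group (N = 117). The within-participant correlation ρ is not given, so it is varied as an assumption from 0 to 0.9. Tests are two-sided where that applies, sphericity is assumed, and required totals are rounded up to a multiple of 3.

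**Formulas (noncentral F, noncentrality λ)**

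- One-way ANOVA: λ = N f², df 2 and N − 3.
- Repeated measures, between groups: λ = N f² m / [1 + (m − 1)ρ], df 2 and N − 3.
- Repeated measures, group by time: λ = N f² m / (1 − ρ), df 4 and 2(N − 3).

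**Attempt 1: f = 0.71 (f² = 0.5041)**

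| Test | λ at required N | Required total N | Power at that N |
|---|---|---|---|
| One-way | 36 × 0.5041 = 18.1 | 36 | 96.2% |
| Between, ρ = 0 | 15 × 0.5041 × 3 / 1 = 22.7 | 15 | 96.9% |
| Between, ρ = 0.5 | 27 × 0.5041 × 3 / 2 = 20.4 | 27 | 97.4% |
| Between, ρ = 0.9 | 36 × 0.5041 × 3 / 2.8 = 19.4 | 36 | 97.2% |
| Group by time, ρ = 0.5 | 12 × 0.5041 × 3 / 0.5 = 36.3 | 12 | 99.5% |

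All are far below 117. At N = 117, the one-way power is about 100%.

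**Attempt 2: d = 0.71, two arms, two-sided 5%**

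Normal approximation: n = 2(1.960 + 1.751)² / 0.71² = 54.6, so 55 per group. The exact noncentral t gives 56 (power 96.1%; 55 gives 95.8%). With 39 per group, power is 87%.

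**Attempt 3: d = 0.71 converted to f, between-groups effect over three visits**

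| Conversion | f | ρ needed | λ at N = 117 | Power |
|---|---|---|---|---|
| d/2 | 0.355 | 0.80 | 117 × 0.1260 × 3 / 2.60 = 17.0 | 96.3% |
| d√2/3 (one arm differs from the other two) | 0.335 | 0.67 | 117 × 0.1122 × 3 / 2.34 = 16.8 | 96.1% |
| d/√6 (third arm midway) | 0.290 | 0.38 | 117 × 0.0841 × 3 / 1.76 = 16.8 | 96.0% |

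Each pair gives N = 117, so the stated figure can be reached. Both the conversion and the correlation have to be supplied by the reader, and three different pairs fit equally well.

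**Which effect does attempt 3 power?** The between-groups effect averages T1, T2 and T3. Section 2.4 places the questionnaires before the session at each visit, so T1 is a pre-intervention measurement. The primary outcome, change from T1 to T3, is a group-by-time question. For f = 0.355, the group-by-time test needs 57 in total at ρ = 0 and 15 at ρ = 0.8, not 117.

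**What 129 delivers**

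- Evaluable per group at 12% loss: 43 × 0.88 = 37.8, about 38.
- Unadjusted two-sample t, two-sided 5%, 80% power, n = 38: d = 0.65.
- 95% CI half-width: 1.993 × √(2/38) = 0.457, about 0.46 SD.
- Power if d = 0.71: 86% at 38 per group, 87% at 39.

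**The case against.** The strongest reply is that the stated size is not impossible. Attempt 3 uses the analysis family named in section 3.2 and the three visits named in section 3.1, and it gives 117. That stands: a reader might infer that no standard reading yields 39 per group, and that is too strong. What remains is that the route needs a correlation that the same section says could not be estimated, and that it powers an effect other than the primary outcome.

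Two further routes come close but cannot be shown from the article. By one-way ANOVA with f = 0.71, 39 participants in total have 97.5% power, so a total may have been misread as a per-group figure. And 71% as a proportion against an assumed 30% needs 38 per group, but the article gives neither a comparator rate nor a binary endpoint.

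A reader might also infer that the comparison of Group A with Group B has far less than 96% power. The article does not support this. Power of 86% to 87% holds only if 71% means d = 0.71 and the test is an unadjusted two-sample comparison at 5%. With baseline adjustment, the effective d is 0.71/√(1 − r²), and power at 39 per group is about 95% for an assumed baseline correlation r of 0.5 and 97% for 0.6. Lower figures need a stricter alpha, and section 3.1 states only 5%.

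Finally, an article condenses the full protocol, which may hold the G*Power settings. That could explain the missing metric and test. It does not remove the conflict between two statements printed in consecutive paragraphs. The article also discloses the feasibility basis, and the randomization, endpoint and analysis are unaffected.

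**Conclusion.** The point holds in two parts. First, section 3.1 contradicts itself on whether a power calculation could be done; this needs no assumption. Second, 39 per group at 96% power cannot be reproduced from the stated inputs. Read directly, 0.71 requires 36 or fewer in total as f (one-way or repeated-measures between-groups; 12 in total for group by time at ρ = 0.5), or 56 per group as d. N = 117 appears only after adding an unstated conversion and a correlation of about 0.4 to 0.8, and then for the visit-averaged group effect rather than the T1-to-T3 change.

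This does not show that the trial is underpowered. Its true power is unknown, because the article supports no effect size. The finding is that the 96% has no traceable basis. The f-based figures rest on sphericity and the stated range of ρ, and the pairwise figures on an unadjusted two-sided t-test at 5%.

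**What to change.** In section 3.1, delete the 71% effect size and the 96% power, and keep 129 as a feasibility size. Then state what that size delivers. At the planned 12% loss, about 38 per group are evaluable, giving about 80% power for an unadjusted pairwise standardized difference of about 0.65 (two-sided 5%) and a 95% CI half-width of about 0.46 SD. Label any power quoted for d = 0.71 as conditional on that reading: about 86% at 38 per group and 87% at 39.

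If the authors prefer to keep a power statement, they would need to give the effect-size metric and its source, the G*Power test, and the correlation. They would also need to show that the test matches the primary outcome and withdraw the sentence saying that no formal calculation could be done.

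The cost is a rewording of one section. The stated power becomes less favourable; the number of participants does not change.

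### The final sample of 129 (43 per group) is a 10.3% addition to 39 per group, not the stated 12%, and keeps 39 evaluable only if losses stay at or below 9.3%

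*Protocol article*

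**What the plan says.** All the relevant figures are in section 3.1 (The Sample Size) of the protocol article.

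- Size before any allowance for loss: "The sample size was determined to be 39 participants per group". For the whole trial, "the total number of participants would be 117, categorized into three groups of 39 participants each".
- Allowance: "12% was added to the final value of 39 participants, resulting in a final sample of 129 participants".
- Allocation of the final sample: "The total number of participants in each group was 43".
- Expected attrition, in words only: the section describes palliative oncology as a setting where "recruitment is inherently limited and attrition rates are high".

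The article gives no other loss rate and no rounding rule.

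**The concern.** The sentence on loss to follow-up links three numbers: 39, 12% and 129. A reader can check it in one line, and it does not come out. The final sample is smaller than the stated percentage produces, whether the 12% is added to 39 or 39 is treated as the number that must remain after a 12% loss.

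What is at stake is the margin for attrition that a reader takes from the paragraph. The primary outcome in section 2.6 is the change in worst pain from T1 to T3 at eight weeks, so a participant lost before T3 has no observed value for it. The Discussion names abandonment of home practice and death as likely causes of loss. The paragraph reads as if the design can lose 12% and still have 39 per group. It cannot quite do so. The sample-size statement is also likely to be carried into the results report, where the same three numbers would again disagree.

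**Working it through.** **Inputs, all from section 3.1:** 39 per group and 117 in total before the allowance; 12% allowance; 43 per group and 129 in total after it; three equal groups.

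**1. Reproducing the stated figure.** The wording describes an addition, n × (1 + 0.12):

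- per group: 39 × 1.12 = 43.68
- in total: 117 × 1.12 = 131.04

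The stated 43 appears only if 43.68 is rounded down, and 3 × 43 = 129. That is the probable origin of the figure, although the article does not say so. Rounded up, as is usual for a sample size, 43.68 becomes 44 per group and 3 × 44 = 132.

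**2. What 12% loss requires.** To have n evaluable after a proportion d is lost, enrol n / (1 − d):

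- per group: 39 / 0.88 = 44.32, so 45, and 3 × 45 = 135
- in total, before rounding to equal groups: 117 / 0.88 = 132.95

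The additive figure of 44 does not quite reach the target either: 44 × 0.88 = 38.7.

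**3. What 129 contains.**

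- increase: 43 / 39 = 129 / 117 = 1.1026, that is 10.3%
- tolerable loss: 1 − 39/43 = 4/43 = 9.3%

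**4. What remains from 129 at 12% loss.**

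- per group: 43 × 0.88 = 37.84, against 39
- in total: 129 × 0.88 = 113.52, against 117

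If each participant is lost independently with probability 0.12 (an assumption), the probability that a given group keeps at least 39 is about 0.40 with 43 enrolled, 0.56 with 44 and 0.71 with 45.

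**Summary**

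| Basis | Per group | Total | Expected to remain per group at 12% loss |
|---|---|---|---|
| As stated | 43 | 129 | 37.8 |
| 39 × 1.12, rounded up | 44 | 132 | 38.7 |
| 39 / 0.88, rounded up | 45 | 135 | 39.6 |

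**5. Effect on power.** The article does not define the scale of its effect size, so an illustration needs an assumption. For a two-sample t-test between two groups (two-sided 5%, 80% power), the detectable standardised difference is 0.643 SD with 39 per group and 0.651 SD with 38, a change of less than 0.01 SD. This comparison is not the planned analysis, which section 3.2 gives as repeated-measures ANOVA or GEE. It serves only to show how little one participant per group matters.

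**The case against.** The strongest reply is that this is a rounding slip. On the article's own additive method the final sample is short by one participant per group, 129 against 132, or 2.3%. That stands, and it sets the weight of the point.

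A second reply is that the article never promises 39 evaluable after exactly 12% loss. It says only that a percentage was added with possible loss in mind. Adding the percentage is a common convention, slightly too generous to the design, and 45 per group answers a target that the reader infers. This stands in part. Division is the operation that protects the 39, but the clear contradiction is between 43 and 44, and it exists without division.

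A third reply is that the 39 is itself weakly supported, because the same section says that no formal power-based calculation could be conducted. Missing such a target by about one participant then has little inferential consequence. That is fair. The basis of the 39 is a separate matter, and it does not make the three numbers agree.

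A reader might go further and infer that the trial has no real protection against attrition, or that it loses material power. The documents do not support that. The design has most of the stated protection: it tolerates 9.3% loss where 12% is implied. A larger loss in power appears only under a higher attrition rate, and the article gives none. Most of any such loss would remain even with 44 or 45 per group, so it cannot be charged to this error.

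**Conclusion.** The point holds as a minor error in a stated figure. The sample of 129 falls short of the 12% allowance on both readings: by 3 participants (1 per group) if 12% is added and rounded up, and by 6 (2 per group) if 39 is to remain after 12% loss. At the protocol's own loss rate the expected evaluable number is a little over one per group below target, with a negligible effect on power.

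The arithmetic takes the 39, the 12% and equal groups as given. It needs no assumption beyond that, except for the retention probabilities (independent losses) and the power illustration (a pairwise t-test), neither of which the conclusion depends on. No other part of the article repairs the discrepancy.

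**What to change.** Restate the sentence in section 3.1, for example: *129 participants (43 per group), a 10.3% addition, retain 39 evaluable per group if losses do not exceed 9.3% (4 of 43); at 12% loss about 38 per group are expected.*

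This is a rewording. It changes neither enrolment nor the design, and its only cost is that the stated margin for loss becomes slightly less favourable. The same corrected figures should be used when the sample size is described in the results report.

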### 3.2. Analysis

Descriptive statistics are applied to characterize patients at baseline. Continuous variables are reported as the mean and standard deviation, while categorical variables are expressed as frequency and percentage. To analyze the longitudinal data of the three groups, repeated-measures ANOVA is used to define the impact of each intervention on the three paired groups of participants. The response variable, which is mindfulness meditation through virtual reality, is analyzed over time, comparing the three groups. If we do not have a normal sample, we will perform the analysis of Generalized Estimating Equations (GEEs), a semi-parametric method to test the differences between groups and the interaction of variables and groups over time.

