While the existing literature demonstrates the benefits of VR in chronic pain contexts, with significant reductions in pain intensity, psychological distress, and functional disability, the present protocol seeks to expand this discussion of evidence to a scenario that has been little explored: cancer pain in palliative care [25,26].

Another aspect to consider is the emotional and psychological state of patients. Evidence indicates that emotional distress acts as a modulator of pain perception and response to non-pharmacological interventions [9]. Meditation can promote significant improvement in quality of life, as demonstrated even in populations with high psychological morbidity [10,23]. However, for these benefits to remain consolidated, continuous practice is essential, which makes adherence a critical variable.

Moreover, the extant literature acknowledges that in randomized trials, equivalence of duration between groups is not a methodological requirement. Consequently, these groups are capable of participating in sessions of varying durations, as the duration of interventions is no longer regarded as a limitation, in contrast to conventional mindfulness programs [26]. Studies have demonstrated that there are no substantial discrepancies between the short-term and long-term consequences of interventions that utilize brief meditation techniques to enhance well-being [27].

This scenario should be carefully considered in the final analysis of the results, since differences observed between modalities may reflect both the intrinsic effectiveness of each meditation format and the ability of each patient to maintain the proposed practice. Future research should explore strategies to optimize adherence, such as active remote support, hybrid sessions (in person and at home), or personalized adaptations to the patient’s clinical profile.

It is important to note that this protocol is vulnerable to certain limitations, particularly in cases involving patients receiving palliative care in the terminal phase of the disease. These limitations may include loss to follow-up due to death, the emergence of uncontrollable pain from disease progression, and the combination of pharmacological therapies such as chemotherapy, which can cause side effects and symptoms that are complex to manage.

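### The named repeated-measures ANOVA normally keeps only patients seen at T1, T2 and T3, so in a trial that expects high attrition it wastes observed data, and could bias the arm difference if dropout differs by arm

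*Protocol article*

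**What the plan says.** Section 3.2 (Analysis) fixes the longitudinal method: "To analyze the longitudinal data of the three groups, repeated-measures ANOVA is used". One alternative is given, with one trigger: "If we do not have a normal sample, we will perform the analysis of Generalized Estimating Equations (GEEs". Nothing in that section ties the choice of method to missing visits.

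Section 2.6 (Outcome Measures) defines the primary outcome as the change in the BPI worst-pain item "from the beginning of the study (T1) to the eight-week follow-up (T3"). T2 plays no part in that definition, although the schedule comprises "longitudinal assessments at T1 (baseline), T2 (four weeks), and T3 (eight weeks").

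Section 3.1 (The Sample Size) describes palliative oncology as a setting "where recruitment is inherently limited and attrition rates are high" and makes one numerical allowance: "12% was added to the final value of 39 participants, resulting in a final sample of 129 participants". It also says that "the analyses would be performed in SPSS (version 29.0"). The Discussion lists among the trial's limitations "loss to follow-up due to death, the emergence of uncontrollable pain from disease progression", followed by a third item, the concurrent use of drug therapies such as chemotherapy.

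**The concern.** Classical repeated-measures ANOVA works on a complete row of T1, T2 and T3 for each patient, and the usual SPSS repeated-measures procedure removes any patient with a gap. Two kinds of patient are then lost. One has T1 and T3 but missed T2: the primary outcome is fully observed and is not used. The other has T1 and T2 but not T3: there is no observed T1-to-T3 change, but the T2 score carries information about T3 that a model using all visits would exploit.

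At stake is first precision, in a trial of 43 per arm. Second, the comparison becomes one of patients who attended every visit and not of the groups as randomised. That can shift the arm difference if the patients who leave differ systematically between arms.

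**Working it through.** **Inputs from the article.** 129 randomised, 43 per arm; overall loss allowance 12% (Section 3.1). Primary outcome needs T1 and T3 only (Section 2.6).

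**The plan's own figure.** 39 × 1.12 = 43.68, taken as 43; 43 × 3 = 129.

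**Assumed.** The article gives no rate of missing T2 or T3 separately. Let each follow-up visit be missed independently with probability p, and T1 be complete.

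- T3 observed, so primary outcome known: 129 × (1 − p)
- All three visits, so kept by the ANOVA: 129 × (1 − p)²
- Primary outcome known but discarded (T2 missed, T3 attended): 129 × p × (1 − p)

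| p | T3 observed | All visits | Known outcomes discarded |
|---|---|---|---|
| 5% | 122.5 | 116.4 | 6.1 |
| 12% | 113.5 | 99.9 | 13.6 |
| 20% | 103.2 | 82.6 | 20.6 |

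Per arm at p = 12%: 43 × 0.88² = 33.3 with all visits, 43 × 0.88 = 37.8 with T1 and T3, and 43 × (1 − 0.12²) = 42.4 with at least one follow-up visit.

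**The other extreme.** If all loss is permanent, everyone seen at T3 was also seen at T2. The last column is then zero at any loss rate, and only the T1-and-T2 patients are wasted.

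**Bias.** A simulation used 43 per arm, SD 2.2, correlation 0.6, a true A−C difference of 1.0 point, 2,000 runs per scenario, and permanent dropout depending on the pain already observed. All these settings are assumptions. It compared the complete-case T1-to-T3 difference with a likelihood estimate from all observed visits.

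| Baseline dropout per visit | Complete-case bias, same mechanism in all arms | Complete-case bias, mechanism differs by arm |
|---|---|---|
| 6% | 0.00 | 0.06 to 0.11 |
| 12% | 0.00 | 0.11 to 0.17 |
| 20% | 0.01 | 0.17 to 0.27 |

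Biases are absolute sizes in points; the direction depends on the assumed scenario. The likelihood estimate was off by at most 0.015 throughout. When dropout is unrelated to pain, 6% per visit leaves 0.94² = 88% complete, close to the plan's 12% overall loss; 12% and 20% per visit leave 77% and 64%.

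**Precision under permanent loss.** With dropout unrelated to pain, the SDs of the estimated difference (complete-case against likelihood) were 0.487 and 0.471 at 12% per visit, and 0.535 and 0.501 at 20%. The variance ratios are (0.487/0.471)² = 1.07 and (0.535/0.501)² = 1.14. The gain is real but modest when T2 misses are not intermittent.

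**The case against.** Much can be said for the plan, and most of it limits the size of the point without removing it.

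*Section 3.2 never mentions deleting incomplete cases, and missing-data rules commonly sit in a SAP.* True: deletion is inferred from the usual form of the method. But the method itself is stated, and a SAP would have to replace it, not merely add detail.

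*The discarded outcomes may not exist.* They require patients who miss T2 and return for T3, at a rate that the article does not give. This stands, and is why the range starts at none.

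*Bias needs dropout that differs by arm.* This also stands. With dropout after worsening of 20% against 30%, a second simulation under assumed settings gave 0.06 to 0.08 points, against a standard error near 0.5. Groups A and B use the same 2D home video, so the article gives no obvious reason for a large A−B imbalance.

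*The fallback may be used anyway.* The outcome is one bounded integer item. Under an assumed distribution, a Shapiro-Wilk test rejected normality in all samples of 129 and in 34% of samples of 43. The article does not say how normality will be judged, so which model will be primary is unknown in advance. That is a reason to fix the model, not to leave the rule alone.

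A reader might infer that the Discussion says worsening pain drives dropout, and so contradicts what GEE assumes. It does not: death-related loss, uncontrollable pain and concurrent therapies are listed as separate limitations. Nor has GEE been shown to fail here. With dropout after worsening of 10-20% in A and 50% in controls, exchangeable GEE was off by 0.016 while complete cases were off by 0.18 to 0.23; dropout driven by a high T2 level was not tested. GEE's general theory makes stronger demands on the missingness than likelihood does, but that is a reservation, not a demonstrated harm.

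A reader might also infer that the same-day ESAS change at T1 is lost for non-returners. Table 3 lists the immediate change as its own metric, and nothing makes it depend on later visits.

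**Conclusion.** The point holds as a recommended improvement. The stated method, in its usual form, fits poorly with an outcome that does not need T2 and with a population in which the article expects high attrition and deaths. The main consequence is lost precision: between none (all loss permanent) and about 21 (20% missed independently per visit) observed primary outcomes discarded from 129, and about 14 if 12% is applied to each visit. Patients with T1 and T2 only are wasted in either case.

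Bias in the arm difference is conditional. It is near zero if dropout works the same way in all arms, and about 0.1 to 0.3 points at 12-20% per visit if it does not. Visit-specific missing rates, SD, correlation and dropout mechanisms are all assumptions. The documents do not support the stronger conclusion that the planned comparison will be biased.

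**What to change.** In Section 3.2, make the primary analysis a likelihood-based linear mixed model for repeated measures that uses all observed visits of all randomised patients. Specify arm-by-visit means, an unstructured covariance matrix and a small-sample degrees-of-freedom method such as Kenward-Roger. Read the A−B and A−C differences at T3 from it. Remove the rule that switches models on normality, so that the primary model is fixed before the data are seen.

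Report deaths and dropout by arm beside the result. Keep the complete-case analysis as a sensitivity analysis. Add a sensitivity analysis for informative dropout, because the mixed model assumes data missing at random and does not by itself resolve loss through death.

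The cost is a change of wording and a slightly more complex model to report. Mixed models are available in SPSS, which the plan already names, and no extra patients, visits or data are needed. The change should be made before outcome data are analysed, so that it cannot appear driven by results.
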